# Study protocol for a randomised placebo-controlled trial of pramipexole in addition to mood stabilisers for patients with treatment resistant bipolar depression (the PAX-BD study)

**DOI:** 10.1186/s12888-021-03322-y

**Published:** 2021-07-05

**Keywords:** Bipolar disorder, Treatment resistant bipolar depression, Pramipexole, Mood stabilisers

## Abstract

**Background:**

Treatment Resistant Bipolar Depression (TRBD) is a major contributor to the burden of disease associated with Bipolar Disorder (BD). Treatment options for people experiencing bipolar depression are limited to three interventions listed by National Institute for Health and Care: lamotrigine, quetiapine and olanzapine, of which the latter two are often not well tolerated. The majority of depressed people with BD are therefore prescribed antidepressants despite limited efficacy. This demonstrates an unmet need for additional interventions. Pramipexole has been shown to improve mood symptoms in animal models of depression, in people with Parkinson’s Disease and two proof of principle trials of pramipexole for people with BD who are currently depressed.

**Methods:**

The PAX-BD study, funded by the United Kingdom (UK) National Institute for Health Research, aims to extend previous findings by assessing the efficacy, safety and health economic impact of pramipexole in addition to mood stabilisers for patients with TRBD. A randomised, double-blind, placebo controlled design is conducted in a naturalistic UK National Health Service setting. An internal pilot study to examine feasibility and acceptability of the study design is included. Participants with TRBD are screened from National Health Service secondary care services in up to 40 mental health trusts in the UK, with the aim of recruiting approximately 414 participants into a pre-randomisation phase to achieve a target of 290 randomised participants. Primary safety and efficacy measures are at 12 weeks following randomisation, with follow up of participants to 52 weeks. The primary outcome is depressive symptoms as measured by Quick Inventory for Depressive Symptomatology – Self Report. Secondary outcomes include changes in anxiety, manic symptoms, tolerability, acceptability, quality of life and cost-effectiveness. Outcome measures are collected remotely using self-report tools implemented online, and observer-rated assessments conducted via telephone. ANCOVA will be used to examine the difference in rating scale scores between treatment arms, and dependent on compliance in completion of weekly self-report measures. A mixed effects linear regression model may also be used to account for repeated measures.

**Trial registration:**

ISRCTN72151939. Registered on 28 August 2019, http://www.isrctn.com/ISRCTN72151939

**Protocol Version:** 04-FEB-2021, Version 9.0.

**Supplementary Information:**

The online version contains supplementary material available at 10.1186/s12888-021-03322-y.

## Background

Bipolar disorder (BD) has a lifetime prevalence of 2.5% [1] and is associated with an 8–12 year reduction in life expectancy [2]. People with BD are symptomatic around 50% of the time, the vast majority of which is depression [3, 4] for which National Institute for Health and Care (NICE) guidelines list 3 treatments: lamotrigine, quetiapine, & olanzapine (with or without fluoxetine) [5]. Quetiapine and olanzapine are often not well tolerated due to weight gain and sedation [6, 7]. In part because of the limited number of medication options, around 70% of people with bipolar depression in the United Kingdom (UK) are taking at least one antidepressant [8] despite evidence that they lack efficacy [5], demonstrating a need for extra therapeutic options.

There is a lack of a consensus definition of what constitutes Treatment Resistant Bipolar Depression (TRBD) [9]. However, around 50% of people remain depressed at six months, and 30% at one year because of non-response, intolerance, or non-acceptance of treatment [10], suggesting that TRBD is the major contributor to the enormous burden of disease associated with BD, with an estimated annual UK BD costs of £5.2B, with direct National Health Service (NHS) costs of £342 M at 2010 prices [11, 12].

The potential role of pramipexole as a treatment for depressive episodes in BD is supported by antidepressant-like effects of pramipexole in animal models such as stress-induced suppression of sucrose intake in rats [13], the forced swim test [14, 15], social interaction test [15] and olfactory bulbectomised rats [16]. It has also been shown to increase hippocampal neurogenesis [12], an effect believed to be common to antidepressants [17, 18]. In humans, pramipexole has extensive evidence for in the treatment of Parkinson’s disease [19], for which it has a marketing licence. A meta-analysis of pramipexole in Parkinson’s disease reported an improvement in depressive symptoms on the Unified Parkinson’s Disease Rating Scale [20]. A subsequent 12-week randomised double-blind placebo-controlled trial of pramipexole in people with Parkinson’s disease and significant depressive symptoms reported a significant benefit independent of any motor improvements seen [21]. Such findings, together with hypothesised roles for a hypo-dopaminergic state underlying bipolar depression [22] and naturalistic and open trial data [23–29] led to two small Randomised Controlled Trials (RCT) in bipolar depression [30, 31]. Goldberg et al studied 22 people with mainly type I BD [30] who had failed to respond to at least two adequate trials of standard antidepressants during the current episode. They were given pramipexole or placebo in combination with lithium or anticonvulsant mood stabilisers, and mean improvement in mood scores at six weeks were 48% for pramipexole and 21% for placebo (*p* = 0.05). Zarate and colleagues’ RCT included 21 people with BD type II [31]who had failed at least one trial of a standard antidepressant. 60% of people treated with pramipexole achieved a treatment response at six weeks, compared with 9% taking placebo (*p* = 0.02).

### Aims

The PAX-BD study is a randomised, double-blind, placebo controlled trial of pramipexole in addition to mood stabilisers for patients with treatment resistant bipolar depression, in a UK NHS population, with the aim of assessing the efficacy and safety of pramipexole and collecting health economic data. PAX-BD is funded by the National Institute for Health Research (NIHR) Health Technology Appraisal (HTA) panel.

### Objectives and measures

A key design feature of the PAX-BD study is that outcome measures are mainly collected remotely, mostly using self-report tools implemented on-line using the True Colours platform [32]. Three scales, the Quick Inventory for Depressive Symptomatology – Self Report (QIDS-SR) [33], Altman Self-rating Scale of Mania (ASRM) [34] scale and Generalised Anxiety Disorder-7 (GAD-7) [35] scale are completed on-line by participants weekly from recruitment into the pre-randomisation phase through to the end of follow up. To facilitate comparison of PAX-BD with other studies, the clinician-rated version of the QIDS (QIDS-C) [33], the Montgomery-Asberg Depression Rating Scale (MADRS) [36] and the Young Mania Rating Scale (YMRS) [37] are completed by phone by the study Research Assistants (RAs) at two time points. The timings of the administration of assessments is shown in the Schedule of Events (Table 1).

**Table 1 Tab1:** Schedule of Events

	Screening	Pre-randomisation	Screening and Randomisation	0	Treatment weeks (Post-randomisation)																												Tapering (5, 6, 7)	
					1	2	3	4	5	6	7	8	9 to 11	12	13 to 15	16	17 to 19	20	21 to 23	24	25 to 27	28	29 to 31	32	33 to 35	36	37 to 39	40	41 to 43	44	45 to 47	48	49 to 51	52*
Informed consent (1,2)	✓		✓																															
Demographics	✓	✓																																
Eligibility assessment	✓		✓																															
Randomisation			✓																															
RA safety monitoring call (3, 8)		✓		✓	✓	✓	✓	✓	✓	✓	✓	✓	✓	✓		✓		✓		✓		✓		✓		✓		✓		✓		✓	✓	✓
CSO contact (4)						✓				✓				✓						✓						✓						✓		✓
QIDS-SR, GAD-7 and ASRM		✓		✓	✓	✓	✓	✓	✓	✓	✓	✓	✓	✓	✓	✓	✓	✓	✓	✓	✓	✓	✓	✓	✓	✓	✓	✓	✓	✓	✓	✓	✓	✓
SHAPS				✓						✓				✓																				
WSAS				✓						✓				✓						✓						✓						✓		
TSQM										✓				✓		✓		✓		✓		✓		✓		✓		✓		✓		✓		
QUIP-RS				✓						✓				✓		✓		✓		✓		✓		✓		✓		✓		✓		✓		✓
MADRS, QIDS-C and YMRS				✓										✓																				
IMP Dispensings			✓					✓						✓				✓				✓				✓				✓				
Qualitative Interviews		✓												✓																				
Participant Vouchers														✓												✓								✓
Unblinding (9)																																✓		

^[1]^Consent is received to enter the pre-randomisation phase. ^2^ To be randomised to trial medication. ^**3**^ Weekly through pre-randomisation phase and until participant begins trial medication. ^**4**^ CSO or other delegated person at site – this will involve collection of medication returns and urine samples. ^5^ If a participant stops taking medication for any reason during the trial, RA phone calls including Dopamine Agonist Withdrawal Syndrome screening will take place weekly during tapering. If participant has withdrawn from the trial, final safety assessment including pregnancy test for women of child-bearing potential will take place when participant has been drug-free for 2 weeks. ^6^ Final safety assessments will take place at week 52 or when participant has been drug-free for 2 weeks, whichever is later. ^7^Week 49–52 schedule of assessments for tapering not applicable for participants who have been unblinded and are taking placebo. Participants receiving placebo will receive a final ‘thank you’ RA phone call following unblinding medication. No further safety assessments, including pregnancy test, will be undertaken for these participants. ^**8**^ Weekly through tapering phase. ^9^ Unblinding to take place after week 48 assessments only for participants who have indicated that they would wish to continue taking pramipexole after the end of the trial, if they were found to be receiving it. *Plus up to 2 weeks if required

### Primary objective

To evaluate the clinical effectiveness of pramipexole versus placebo alongside standard mood stabilising medication, over 12 weeks, in the management of participants with treatment resistant bipolar depression, assessed using the QIDS-SR [33].

### Secondary efficacy objectives

To examine the impact of pramipexole treatment on mood and anxiety symptoms over 48 weeks, and pleasure symptoms over 12 weeks. In addition to the weekly assessment of depressive and anxiety symptoms with the QIDS-SR and GAD-7 [33, 35] respectively, the ability to experience pleasure is assessed using the Snaith-Hamilton Pleasure Scale (SHAPS) [38] at randomisation and at weeks 6 and 12 post-randomisation.To examine the impact of pramipexole on psychosocial function over 48 weeks, using the self-reported Work and Social Adjustment Scale (WSAS) [39].

### Secondary safety and acceptability objectives

To examine risk of switching to mania and occurrence of psychosis or impulse control disorders, which are known possible side-effects of pramipexole [24], over 48 weeks. Manic symptoms are assessed weekly using an on-line version of the ASRM scale [34]. Rates of impulsivity during the study are monitored using the Questionnaire for Impulsive-Compulsive Disorders in Parkinson’s disease – Rating Scale (QUIP-RS) [40], administered by telephone by the study RAs. Psychosis is not formally rated but is specifically screened for during regular RA phone calls.To examine side effects and overall acceptability of pramipexole treatment over 48 weeks using the Treatment Satisfaction Questionnaire for Medication (TSQM) [41] administered by phone by the study RAs.To examine tolerability of pramipexole by reviewing the rates, severity, seriousness, causality and expectedness Adverse Events (AEs) and Adverse Reactions (ARs).To examine adherence to medication over 48 weeks. Medication is provided to participants by post from the Cumbria, Northumberland, Tyne and Wear (CNTW) pharmacy on seven occasions over the course of the study. Adherence is assessed through a pill count of un-used medication returned by participants at the end of each prescription period.

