### Participants

#### Recruitment

Patients with TRBD are screened and recruited from secondary care services using clinician caseloads, databases and/or research registers in up to 40 mental health trusts across the UK. A list of study sites can be obtained at https://paxbd.org/about/recruiting-sites. Invitation letters and summary leaflets (Supplementary files 1 and 2) are available to advertise to patients directly by post, or channels such as secondary care clinics, websites, social media platforms and patient support groups.

Patients identified by clinicians and/or those showing interest are provided an initial information sheet (Supplementary file 3) in person or via post. Should they wish to proceed, Principal Investigators (PIs) or delegated clinicians take written informed consent (Supplementary file 4) and begin the screening process. Prior to randomisation participants receive a second information sheet (Supplementary file 5) and again are required to provide written informed consent (Supplementary file 6).

Participants who withdraw from the trial are given a withdrawal form (Supplementary file 7) and corresponding end of study information sheet (Supplementary file 8). Withdrawn participants are not replaced. Where a participant no longer wishes to take trial medication and gives consent for continued participation in the trial, they are followed up to 48 weeks. Participants who complete the trial to 48 weeks with trial medication are given the corresponding end of study information sheet (Supplementary file 9). See Fig. 1 for the participant pathway.

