### Intervention

Participants are randomised on a 1:1 basis to receive either pramipexole or placebo. Dosing of study medication is based on doses used in the two previous small pilot studies (*n* = 22; *n* = 21) [30, 31] and, in particular, a naturalistic case series [24]. Dosing occurs in three phases: titration, fixed dose and flexible dose phases. During the titration phase, participants start on a dose of 0.25 mg/daily with 0.25 mg increments every three days to reach the maximum tolerated dose, with a maximum of 2.5 mg/daily, over four weeks. The dose achieved in the titration phase is continued through the fixed-dose phase between weeks 5 to 12 post randomisation. From week 12 to the end of the study, medication is flexibly dosed between 0.25 and 2.5 mg/day, based on the participant’s trajectory of change in mood and tolerability as judged by self-reported measures and side effects.

At 48 weeks, remaining participants are asked whether they wish to continue with pramipexole after the trial if they are found to be taking it; those who do are unblinded to find if they were receiving the drug or placebo. This allows for the immediate withdrawal of participants on placebo, and the continuation of treatment for those receiving pramipexole beyond the study. Participants who wish to discontinue study medication are not unblinded and receive a tapering schedule of a reduction by 0.25 mg every three days, to safely withdraw from trial medication.

Participant’s clinical teams are free to adjust all other medication, though encouraged wherever possible to maintain stability of all medication and doses between randomisation and the 12 week primary outcome point. Participants are provided study diaries at the start of randomisation to guide them through the titration phase, record the dose of medication taken each day, record any changes to concomitant medication and record AEs (Supplementary files 10 and 11). Adherence to the dose schedule is verbally checked with the participant during RA telephone calls.

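### No TSQM is scheduled before week 6 or at discontinuation, so participants who leave the trial earlier contribute nothing to the acceptability comparison

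*Protocol article*

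**What the plan says.** Secondary safety and acceptability objectives assigns the TSQM its task: "To examine side effects and overall acceptability of pramipexole treatment over 48 weeks using the Treatment Satisfaction Questionnaire for Medication (TSQM". Table 1 (Objectives and measures) ticks it at weeks 6, 12, 16, 20 and so on every four weeks to week 48.

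Under Intervention, participants step up their dose "to reach the maximum tolerated dose, with a maximum of 2.5 mg/daily, over four weeks". The dose reached is then held from week 5 to week 12.

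Footnote 5 to Table 1 deals with stopping. It opens "If a participant stops taking medication for any reason during the trial" and provides that "RA phone calls including Dopamine Agonist Withdrawal Syndrome screening will take place weekly during tapering". It continues: "If participant has withdrawn from the trial, final safety assessment including pregnancy test for women of child-bearing potential will take place" after two drug-free weeks. It names no TSQM in either case.

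Recruitment separates stopping medication from leaving the trial, with follow-up counted in weeks: "Where a participant no longer wishes to take trial medication and gives consent for continued participation in the trial, they are followed up to 48". Statistical analysis plans an ANCOVA of TSQM scores and says secondary outcomes are handled much as the primary outcome is. The primary analysis uses complete cases, and multiple imputation is considered if enough data are missing.

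**The concern.** Titration takes each participant up towards the limit of what they can tolerate. That is when a participant who finds the treatment unacceptable may well leave, and no TSQM falls in that period or marks the exit. Intolerance is both a reason to leave and part of what the TSQM measures, so the missing scores are unlikely to resemble the observed ones.

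If more participants leave early for this reason in one arm, that arm's mean TSQM score is raised by their absence. A complete-case ANCOVA omits them. Imputation would have no earlier TSQM value from the same person to work from. An analysis plan cannot restore a rating that was never collected, so the remedy has to be in the schedule.

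**Working it through.** **1. Reading the schedule.** The SHAPS row serves as a check on the column positions, because Secondary efficacy objectives gives its timing in words: "at randomisation and at weeks 6 and 12 post-randomisation". Counting columns puts the SHAPS ticks at 0, 6 and 12, as it should. The same count puts the TSQM ticks at 6, 12, 16, 20, 24, 28, 32, 36, 40, 44 and 48. Titration ends at week 4, so the first rating comes 6 − 4 = 2 weeks after it.

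**2. Who lacks a rating.**

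| Participant | TSQM available under the schedule |
|---|---|
| Withdraws from the trial before week 6 | None |
| Stops medication before week 6, stays in follow-up | Not stated: no exemption from week 6, but no instruction either |
| Stops or withdraws after week 6 | At least one rating was already due; none at exit |

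Only the first row is a certain loss.

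**3. The planning figure for dropout.** The only usable rate is the 20% dropout at 12 weeks under Sample size, power and effect size. The stated sample size is consistent with it:

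- per arm, 2 × (1.960 + 1.282)² × 7² / 3² = 114.4, so 115
- total 230; 230 / (1 − 0.20) = 287.5, so 288, against 290 stated

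**4. How many could be lost by week 6.** Planned loss by week 12 is 290 × 0.20 = 58. The article does not say when within the 12 weeks it occurs, so by week 6 it lies between 0 and 58. Assuming linear accrual:

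- by week 4: 58 × 4/12 = 19.3, about 19
- by week 6: 58 × 6/12 = 29, or 10% of 290

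**5. What this does to the comparison.** Let *p* be the proportion of an arm without a score, and *d* the amount by which their mean would fall below that of participants with a score. The observed mean exceeds the full-arm mean by *p* × *d*. The bias in the difference is therefore *p*₁*d*₁ − *p*₀*d*₀, with 1 for pramipexole and 0 for placebo. It is zero when both *p* and *d* are equal across arms.

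The article gives neither *p* by arm nor *d*. As illustration only, assume a 0–100 scale and *d* = 35 in both arms:

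| Loss, pramipexole / placebo (assumed) | Bias in points |
|---|---|
| equal | 0 |
| 10% / 3% | 3.50 − 1.05 = 2.45 |
| 20% / 5% | 7.00 − 1.75 = 5.25 |

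These rows show how the formula behaves and are not estimates for this trial.

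**The case against.** A reader might infer more: that everyone who stops during titration never rates the drug, so that the TSQM compares only those who tolerated it. The documents do not support that.

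- Participants who stop medication and consent to stay are followed to week 48, and nothing exempts them from the week 6 TSQM.
- Participants who stop after week 6 have already been due at least one rating.
- Some late titration stoppers may still be tapering at week 6. The only taper rate given is 0.25 mg every three days, stated for week 48. If it also applied earlier, stopping at 2.5 mg on day 28 would mean nine further steps × 3 days = 27 days, to about day 55, which is beyond day 42.

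Tolerability also does not rest on the TSQM alone. It has its own objective through adverse events and reactions, recorded from consent and so throughout titration. Research assistant calls are weekly over the early weeks, and the pilot interviews include participants who withdraw before week 12. Adverse event data could also inform an imputation model, so it would be wrong to say that no adjustment can help.

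Finally, nothing in the article is misstated here, and how the TSQM is given off medication could be set out in the full protocol.

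All of this stands and keeps the priority low. It does not remove the point. Adverse event records are not the participant's own rating of treatment, and the interviews belong to the pilot and end at saturation. The article prints both the schedule and the stopping footnote in detail, and neither contains an exit rating.

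**Conclusion.** The point holds in a limited form. No TSQM is scheduled before week 6 or at discontinuation. Participants who withdraw from the trial before week 6 contribute none, and the position of those who stop medication but stay is unstated.

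The number affected is about 29 of 290 if the planned 20% dropout at 12 weeks accrues linearly, and anywhere from 0 to 58 otherwise. Whether this biases the comparison depends on loss, or its relation to acceptability, differing by arm. The article gives no figure for either, so neither a size nor a direction can be asserted. This is a cheap improvement to one secondary measure, of minor priority, and leaves the primary analysis untouched.

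**What to change.** Add to the Table 1 footnote on stopping one TSQM at the first research assistant call after a participant stops trial medication, whatever the reason, worded to refer to the medication just stopped.

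Show the arm comparison with these exit ratings included as a sensitivity analysis, beside the analysis at the scheduled weeks. The exit score need not be carried forward to all later weeks; doing so would be a debatable choice for a 48-week outcome.

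The cost is a footnote, one line of analysis and a few minutes per stopping participant, in a call that footnote 5 already schedules during tapering. Some participants, particularly those leaving the trial altogether, will decline, so selective loss is reduced and not removed. The ratings can only be collected prospectively. No dose or clinical rule changes.

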### Health economic objectives

To examine the quality of life, wellbeing, health and social care and broader societal costs of participants randomised to either pramipexole or placebo. To establish the incremental cost-effectiveness of pramipexole in comparison to placebo over 48 weeks. Assessments are conducted via participant completion of on-line versions of the EuroQoL 5 Dimension 5 Level (EQ-5D-5L) [42] measure of health-related quality of life, and the ICEpop CAPability measure for Adults (ICECAP-A) [43] and the Oxford CAPabilities questionnaire-Mental Health (OxCAP-MH) [44] capturing broader wellbeing, and the Health Economics Questionnaire (HEQ) [45] for information on health and social services utilisation and broader societal costs.

